## Purpose

### Primary objective of the study

This study will evaluate the effectiveness of two innovative knowledge transfer interventions using a quasi-experimental, mixed-methods research design. Specific objectives include:

1. To determine the relative effectiveness of a Stakeholder-Hosted Interactive Problem-based Seminar (SHIPS) and Online Problem-Based tutorials (e-PBL) in changing knowledge, utilization, and integration of knowledge in clinical decision-making.

### Secondary objectives

1. To identify the key elements of SHIPS and e-PBL that engage participants in KT and assist them in addressing barriers to change;

2. To determine whether clinicians exhibit a decisional balance and spectrum of behaviors consistent with the Transtheoretical Model of (Readiness to) Change; and

3. To determine the relative importance of potential predictors of change, including characteristics of clinicians (years of practice, highest degree, Readiness To Change), practice settings (practice type, caseloads, years of experience), and how they affect knowledge acquisition and implementation following KT interventions.

## Method/Design

This study will implement two knowledge transfer interventions at three sites across Canada and determine the intervention effectiveness and its mediators using a mixed qualitative quantitative approach.

### Rationale for a mixed-methods approach

Cochrane reviewers have suggested that a mixed-method approach is required to understand how to change clinical behaviour [22]. This study has a strong quantitative foundation based on specific research questions that will be answered using validated instruments to assess KT outcomes. However, a qualitative approach is needed to augment this information. A qualitative approach will be used to elucidate the specific key elements that enhance or obstruct the effectiveness of these two new KT approaches and to understand the decisional balance that underlies the process of changing clinical behavior in response to knowledge transfer.

### Rationale for phased implementation in three cities

We have recruited three sites across Canada. At each site a clinical partner "host" will assist in recruitment of participants and local organizations. We felt national representation was important to provide generalizable results and to insure that this project facilitates KT networks that will support future national initiatives for broader implementation. We specifically did not use Hamilton, as we felt it was "contaminated" by numerous prior activities conducted by study investigators. The Kitchener-Waterloo site will be the alpha site, with the second wave of KT intervention taking place in Calgary and Halifax. The phased approach has several advantages. For instance, it allows us to train the research assistants from the Calgary and Halifax areas in a central location. Based at McMaster University, the project coordinator will have the primary responsibility for project coordination, with site research assistants sharing site organization and local chart audit evaluation. These research assistants will come to the first KT site to undergo standardized training on the chart audit and chart-stimulated recall procedures. This will insure they have a comprehensive understanding of the interpretation of responses during the chart-stimulated recall. Their orientation will consist of training on the theory and methods of chart-stimulated recall, participation in both KT strategies, and observation of the chart audit (use and stimulated recall) conducted by study investigators at the alpha site. This will insure consistency across the three sites. A further advantage of the phased approach is that we will be able to maximize the value of our qualitative component evaluating the *process *of KT by making changes to qualitative probes as indicated by alpha site results. That is, we will be able to commence the iterative qualitative analysis that will inform further qualitative data collection and analysis, providing an enhanced understanding of how changes in clinical behavior are motivated.

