**Method/Design:**

Physical and occupational therapists (n = 144) will be recruited in partnership with the national professional associations to evaluate two different KT interventions with the same curriculum: 1) Stakeholder-Hosted Interactive Problem-Based Seminar (SHIPS), and 2) Online Problem-Based course (e-PBL). SHIPS will consist of face-to-face problem-based learning (PBL) for 2 1/2 days with outcome measure developers as facilitators, using six problems generated in consultation with participants. The e-PBL will consist of a 6-week web-based course with six generic problems developed by content experts. SHIPS will be conducted in three urban centers in Canada. Participants will be block-allocated by a minimization procedure to either of the two interventions to minimize any prognostic differences. Trained evaluators at each site will conduct chart audits and chart-stimulated recall. Trained interviewers will conduct semi-structured interviews focused on identifying critical elements in KT and implementing practice changes. Interviews will be transcribed verbatim. Baseline predictors including demographics, knowledge, attitudes/barriers regarding outcome measures, and Readiness to Change will be assessed by self-report. Immediately post-intervention and 6 months later, these will be re-administered. Primary qualitative and quantitative evaluations will be conducted 6-months post-intervention to assess the relative effectiveness of KT interventions and to identify elements that contribute to changing clinical behavior. Chart audits will determine the utilization of outcome measures (counts). Incorporation of outcome measures into clinical reasoning will be assessed using an innovative technique: chart-stimulated recall.

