#### Stakeholder-Hosted Interactive Problem-based Seminars (SHIPS)

The SHIPS will consist of a 2 1/2-day interactive PBL sessions with 10 hours of contact/tutorial time and 15–20 hours of facilitated independent group work that will focus on application of learned concepts. Consistent with a problem-based philosophy, small groups of clinicians will participate in interactive sessions facilitated by a faculty tutor. The faculty tutor will be a developer of outcome measures, an expert facilitator in PBL, and one of the study investigators. The SHIPS' knowledge transfer strategy is based on evidence establishing the importance of using opinion leaders with scientific and professional credibility [32], and will be operationalized using our experience in PBL as a method of providing contextualized learning. Six "problems" will be generated by faculty through a consultative process with the participants prior to the sessions. Problems will be generated to reflect the established curriculum, with a problem that represents the practice characteristics and issues expressed by participants. Participants will conduct this process four weeks prior to the SHIPS intervention and will receive the curriculum, course objectives, and a recommended reading list one week prior to attendance at the SHIPS.

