#### Online Problem-based Course (e-PBL)

The web-based intervention will consist of six weekly e-PBL sessions with 10 contact hours and 10–15 facilitated independent learning activities. Six generic problems will be developed by the study investigators to meet the curriculum objectives. The e-PBL will be delivered over a relatively short period (six weeks) as previous research demonstrated a large drop-out rate with 14 weeks [72]. Sessions will be facilitated and monitored by a faculty member who is familiar with web-based instruction, PBL, and has expertise in outcome measures. Study investigators will ensure visibility through their participation in online chats and content development, but the operation of the online delivery will be managed by an educator with expertise in online delivery. The consistent components of each session will be a problem generated by the faculty to represent key concepts regarding outcome measures, session objectives, a recommended reading list, and discussion questions. Discussion questions will be addressed through asynchronous online chat amongst participants, as facilitated by faculty tutors.

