##### 3) Integration of knowledge

The integration of knowledge into clinical decision-making is more complex than measures of utilization and, hence, more difficult to measure. However, as the ultimate purpose of new knowledge is to improve the quality of care, evaluation of how clinicians use new information to make decisions is critical. Simple measures of the use of concrete behaviors – prescription practices or completion of outcome scales – provide information on whether practitioners are receptive to changing their behavior. However, these measures do not provide insights about whether these altered clinical behaviors are integrated into higher-level clinical reasoning. As reviewed above, these higher-level evaluations are rarely incorporated into KT evaluations [63]. Chart-stimulated recall [75-77] is an evaluation method that combines personal interview and chart audit to engage participants in a reflective discussion on these deeper levels of cognitive reasoning. A trained evaluator draws inferences from the information to rate the clinician's behavior on a variety of items that reflect clinical reasoning and competency in the area of interest. This method was originally developed at McMaster University to evaluate competence in medical practitioners [76], and it has been shown to be a valid process in this population [75,76,78], as well as amongst occupational therapists [77].

The chart-stimulated recall form must be developed specifically for the competencies being evaluated. The competencies evaluated in this study will be the core curriculum about outcome measurements, with an emphasis on their application to clinical reasoning. This focus includes the clinician's ability to provide: a rationale for why specific outcome measures were selected for specific patients, an understanding of the correct application of the scale, an ability to use the obtained score to determine disability and prognosis, and the ability to set rehabilitation goals based on disability scores, including clear parameters for the expected change in scores following intervention. Chart-stimulated recall responses are scored on a seven-item scale that reflects the extent of competency [77]. The staged process of the study design will enable high-quality evaluations during chart-stimulated recall by allowing evaluators from Eastern and Western Canada to participate in Phase 1 of the project as a means of gaining greater consistency between raters.

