The chart-stimulated recall will be conducted by a single trained research assistant assigned to each location. Two of the five charts selected for chart audit will be randomly selected for chart-stimulated recall. The interviewer will ask questions in a semi-structured format that requires specific responses from the therapist, explaining the content and clinical reasoning used for the two patients whose records are used to evaluate the core competencies being tested. The answers are scored on a seven-point scale. The spectrum of information included in the chart-stimulated recall analysis will include all intake assessments, progress notes, and discharge records for a specific patient. A detailed manual on the types of responses required will be developed in conjunction with curriculum development. Chart-stimulated recall will provide a quantitative assessment of the clinical reasoning used with respect to the use of outcome measures in managing specific patients.

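### The protocol conflicts on who rates chart-stimulated recall at the alpha site and describes no masking, so raters of this subjective primary outcome are likely, though not certain, to know the arm

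*Protocol article*

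**What the plan says.** Three places in the protocol article say who collects the chart-based outcomes.

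- Abstract, Method/Design: "Trained evaluators at each site will conduct chart audits and chart-stimulated recall".
- Rationale for phased implementation in three cities: the assistants' orientation includes "observation of the chart audit (use and stimulated recall) conducted by study investigators at the alpha site".
- Study measures, 3) Integration of knowledge: "The chart-stimulated recall will be conducted by a single trained research assistant assigned to each location".

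Other passages bear on what those people would know.

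- SHIPS section: "The faculty tutor will be a developer of outcome measures, an expert facilitator in PBL, and one of the study investigators". Contact is face to face over 2 1/2 days.
- e-PBL section: a separate educator manages the online delivery, but "Study investigators will ensure visibility through their participation in online chats and content development".
- Phased implementation: the project coordinator has the main coordinating role, "with site research assistants sharing site organization and local chart audit evaluation". The assistants' training also includes "participation in both KT strategies".

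On the nature of the measure: "A trained evaluator draws inferences from the information to rate the clinician's behavior on a variety of items". The Quantitative analyses section names the recall score as one of three primary outcomes, with knowledge and utilization. The article describes no masking of the audit or recall raters. The only comparable safeguard is in the qualitative section, where the telephone interviewer is someone the participants do not know.

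**The concern.** An inference-based score is open to the rater's expectations. If the rater knows the arm, and more so if the rater taught some of the therapists being scored, ratings can shift towards one arm. That shift enters the SHIPS versus e-PBL comparison directly, and a larger sample does not remove it.

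Two features of the design add weight. Allocation is by a non-randomised minimization procedure that allows reassignment before participants are told their group, so sound outcome assessment is one of the main remaining protections. And each location has a single recall rater, so no second rating would reveal a shift. The Calgary and Halifax assistants also learn to interpret responses by watching the alpha-site ratings, so a tendency there could be passed on.

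This is more than a detail left out of a condensed article. The text itself assigns roles that make knowledge of the arm likely, and it gives two answers on who rates at the alpha site.

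**Working it through.** **Step 1. Who rates recall at the alpha site.** The phased-implementation section has investigators conducting both parts of the audit there, including stimulated recall. The integration-of-knowledge section gives recall to one assistant per location, without exception. The abstract's wording fits either. As written, the two sections cannot both be the complete rule for the alpha site.

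**Step 2. What each type of rater would probably know.**

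- *Investigator:* an investigator who tutored SHIPS would recognise SHIPS participants. The article does not say that the tutoring and auditing investigators are the same individuals, so this is probable for some and certain for none.
- *Assistant:* shares site organisation and is not said to be masked. No sentence gives assistants allocation or attendance lists. Knowledge of the arm is plausible but inferred.

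**Step 3. Which outcomes are exposed.**

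- *Knowledge:* multiple-choice test, with little room for rater judgement.
- *Utilization:* counts from completed forms in randomly chosen charts, recorded on a standardized extraction form. Less exposed.
- *Recall:* a seven-point rating drawn from an interview. The most exposed.

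**Step 4. The plan's own sample size.** Inputs from Sample size requirements: two-sided alpha 0.05, effect size 0.50, 64 per group. The section labels 0.80 as the Type II error, but its figure reproduces with 0.80 as power. A two-sample t-test needs 63.8, so 64 per group, and 64 gives power 0.801. Then 2 × 64 = 128, and 128/0.9 = 142.2, rounded in the plan to 144, or 48 per site. The concern does not alter this calculation.

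**Step 5. Illustrative effect of a rating shift.** The documents give no rater-bias figure, so the shifts are assumptions. Suppose no true difference and ratings shifted by *b* SD towards one arm. With *n* = 64 per arm:

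- δ = b × s × √(n/2) = b × s × √32 = 5.657 × b × s, where *s* is the share of participants affected (1 for all sites; 48/144 = 1/3 for the alpha site alone, assuming equal dropout across sites).
- False-positive rate ≈ Φ(δ − 1.96) + Φ(−δ − 1.96).

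| Shift b (SD) | All sites: δ | Rate | Alpha site only: δ | Rate |
|---|---|---|---|---|
| 0.1 | 0.566 | 8.7% | 0.189 | 5.4% |
| 0.2 | 1.131 | 20.5% | 0.377 | 6.6% |
| 0.3 | 1.697 | 39.6% | 0.566 | 8.7% |

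The noncentral t distribution (126 degrees of freedom) gives 8.7%, 20.2% and 39.2% for all sites, and 5.4%, 6.6% and 8.7% for the alpha site alone. Rounded: about 9%, 20% and 39%, and about 5%, 7% and 9%.

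**The case against.** The strongest reply is that the investigator passage sits in a description of training. It can be read as investigators demonstrating the procedure while the alpha-site assistant produces the study scores. It does not say that investigators score all 48 alpha-site participants, or any fixed number. This stands. A reader might infer that one third of the sample is rated by its own tutors; the documents do not support that.

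Second, a reader might infer that investigators know only the SHIPS arm. They also appear in the e-PBL chats, so the contact differs in mode and intensity and is not confined to one arm. This also stands.

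Third, a reader might infer that the assistants know who attended which course. The coordinator leads coordination, a local host assists, and the assistants' time in both interventions is part of their training at the first site, so it does not reveal allocation at Calgary or Halifax. Nor do they teach either arm, so no direction of bias is shown there. This stands too: a same-direction shift at all sites is an assumption. What remains is that nothing described keeps the allocation from them.

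Fourth, a detailed response manual is planned for recall. That limits discretion but does not mask the rater.

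Last, the full protocol may describe masking. It may, so silence alone would be weak evidence. It does not settle the conflict between the two sections, which is in the published text.

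**Conclusion.** The point holds in a limited form. The article contradicts itself on who rates recall at the alpha site. On either reading, the people named have roles that make knowledge of the arm likely, and no masking is described. The exposure is mainly to the recall score; audit counts are less affected and the knowledge test hardly at all.

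The size is unknown. The illustration runs from about 5% to 9% false positives if assumed shifts of 0.1 to 0.3 SD occur at the alpha site alone, and from about 9% to 39% if the same shifts occur in one direction at all sites. It rests on 64 analysed per arm, no true difference, and equal site shares. A higher figure for the alpha site alone is tempting: about 15% needs a 0.5 SD shift there, which equals the whole effect the trial is sized to detect, and nothing in the documents supports a shift that large. The documents also do not show that raters will in fact know the arm. The case for acting is that the protection costs little and that a score given in an unmasked interview cannot be masked afterwards.

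**What to change.** 1. Reconcile the phased-implementation and integration-of-knowledge sections. State that the alpha-site research assistant, and no investigator or tutor, produces the recall scores used in the analysis. Any ratings that investigators make as demonstrations are excluded from the analysis.
2. Keep allocation and attendance lists with the project coordinator and the local host, and take those tasks away from the rating assistants.
3. State that raters are not told the allocation, and ask participants not to mention their course during recall.

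This should be settled before the first alpha-site ratings.

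The cost is a short protocol change and a re-division of some tasks; the assistants, coordinator and host are already in the plan. Masking will be imperfect, because participants may still reveal their arm.

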### Subjects

#### Recruitment

Participants will be recruited from the surrounding clinics/organizations through existing communications links (e.g., professional newsletters, listservs, and local meetings) and through letters of invitation distributed to eligible clinics in the three cities. In addition, the professional associations have agreed to assist with recruitment though websites and advertisements. Based on our previous projects and pilot work, we anticipate high levels of participation.

#### Inclusion/exclusion criteria

A valid license to practice physical or occupational therapy, and ability to communicate in English is required. Volunteers will be required to complete a knowledge pre-test in the format of a multiple-choice questionnaire. Those who are already knowledgeable, as determined by a score of 75% or greater, will be excluded to avoid ceiling effects (pilot work suggests this will be rare).

#### Sample size requirements

Given that this study is a mixed-methods design, the sample size was based on the quantitative analyses as these have larger sample size requirements. Sample size estimation was based on detecting an effect of 0.50 between groups on any of the three aspects of outcome (knowledge, utilization, and integration into clinical reasoning). Assuming Type I error = 0.05 (2-tailed); Type II error = 0.80; Effect size = 0.50, the sample size required per group = 64. The sample size required for two-comparison groups = 128 and accounting for a 10% dropout = 128/0.9 = 142. We anticipate low dropouts given the priority of continuing education by both professions. We will round our sample size up to 144 to provide a number equally divided between three sites, requiring 48 per site. Based on the need to allocate participants in blocks to interventions and to balance professions and clinical areas evenly, we expect to accommodate 24 participants per intervention group, per site. These will consist of three tutorial groups of eight therapists/groups. Given the distribution of practice patterns in rehabilitation, we expect two groups on orthopedics and one group on pediatric practice at each location. Groups will be formed according to practice settings to insure that the stakeholders can develop "problems" that simulate their own clinical settings/populations.

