## Analyses

### Quantitative analyses

All data will be double-entered in SPSS 14.0. Descriptive analyses will be conducted, including checking for outliers, normality testing, and univariate correlations. The first primary analysis (Objective 1) will be a two-way repeated measures analysis of variance to determine primary unadjusted differences in absolute scores over time, and between groups for each of the three primary outcome measures: knowledge, utilization, and chart-stimulated recall scores. An analysis of covariance will be used to compare these same effects adjusting for baseline knowledge score, Readiness to Change, years of practice, and educational preference. These analyses across the e-PBL and SHIPS groups will determine the relative effectiveness of these two alternative knowledge transfer choices. Effect sizes and their 95% confidence intervals will be calculated to determine whether there are differential impacts on change in knowledge, utilization, and integration of knowledge between the two different KT approaches. For the secondary research question (Objective 2.3) on the relative importance of KT predictors, a multiple linear regression [79,80] will be used to develop models of how years of practice, educational background, caseload characteristics, educational preferences, or Readiness to Change predict changes in knowledge, utilization, or integration following knowledge transfer interventions, with KT method as a covariate.

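### The sample-size line prints the power (0.80) as the Type II error, and its 0.05 is a per-outcome alpha with no allowance in N for three co-equal primary outcomes

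*Protocol article*

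**What the plan says.** The section on sample size requirements gives the assumptions and the result in one line: "Assuming Type I error = 0.05 (2-tailed); Type II error = 0.80; Effect size = 0.50, the sample size required per group = 64". It describes the target as "detecting an effect of 0.50 between groups on any of the three aspects of outcome (knowledge, utilization, and integration into clinical reasoning"). The total of 128 is then raised to 142 for 10% dropout and rounded up to 144, or 72 per group.

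The section on quantitative analyses plans a repeated-measures analysis of variance over time and "between groups for each of the three primary outcome measures: knowledge, utilization, and chart-stimulated recall scores". It labels this unadjusted analysis the first of the primary analyses. An analysis of covariance then examines the same effects with adjustment for four baseline variables. Effect sizes with 95% confidence intervals are planned for the three outcomes.

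Objective 1 asks about relative effectiveness on the same three outcomes within a single objective. The article names no lead outcome, testing order, division of alpha or joint success rule.

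**The concern.** Two things in the same sentence need attention, and they differ in kind.

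The first is a plain contradiction. A Type II error of 0.80 is a power of 0.20, which does not go with 64 per group at an effect size of 0.50. A reader who takes the line literally would conclude that the trial was planned to miss its target effect four times in five.

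The second concerns what the 0.05 covers. Three outcomes carry equal primary status, and the design target is worded as an effect on any of them. If a significant result on any one were read as showing that one intervention is better, 0.05 would not be the error rate of that claim. The leading outcome could then be chosen after the results are known. An adjustment added later would meet an N that was not sized for it.

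**Working it through.** **Inputs.** From the sample-size section: two-sided alpha 0.05, d = 0.50, 1:1 allocation, 64 per group, 10% dropout, 144 in total. From the quantitative analyses section: three primary outcomes. The article gives no correlations between outcomes, so those below are assumptions. All power figures are for a simple two-group comparison of means, not for the repeated-measures or covariance models.

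**1. Reproducing 64.** Per group, n = 2(z₁₋α/₂ + z₁₋β)²/d².
- Power 0.80 (Type II error 0.20): 2 × (1.960 + 0.842)²/0.25 = 62.8, so 63 by the normal approximation. The exact t calculation gives 64, with power 0.801.
- Type II error 0.80 as printed (power 0.20): 2 × (1.960 − 0.842)²/0.25 = 10.0 (10.006 before rounding), so 11. The exact t calculation also gives 11.

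The planned figure therefore rests on power 0.80 and on the full two-sided 0.05. The totals follow: 2 × 64 = 128, and 128/0.9 = 142.2, which 144 covers.

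**2. Familywise error if any one of three results at 0.05 counts.**
- Independent outcomes: 1 − 0.95³ = 0.143.
- Common correlation, by simulation of one million trivariate normal draws for each value:

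| Assumed correlation | Familywise error |
|---|---|
| 0.3 | 13.6% |
| 0.5 | 12.5% |
| 0.7 | 10.9% |
| 0.9 | 8.4% |

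These figures count one test per outcome and leave out the covariance analysis.

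**3. What adjustment does to power at the planned N.** With alpha = 0.05/3 = 0.0167 two-sided and d = 0.50:
- Power per outcome is 0.66 with 64 per group and 0.72 with 72 per group (no dropout).
- Keeping 0.80 for each outcome would need 86 per group: 172 in total, and 172/0.9 = 191.1, so 192 with dropout, against 144 planned.
- Power to detect at least one outcome, if all three true effects are 0.50 and there are 64 per group, is 0.96 if independent, and 0.92, 0.88 and 0.83 at correlations 0.3, 0.5 and 0.7. The independent case is 1 − (1 − 0.66)³ = 0.96.

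Under Holm, 0.66 is the first-step figure for a given outcome. Later steps use larger alphas and can only raise it.

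**The case against.** A good deal can be said for the plan, and most of it stands.

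- **The 0.80 is a labelling slip.** This is right. The calculation behind 64 used the conventional power of 0.80. A reader might infer that the trial has 20% power or that N is wrong; the arithmetic supports neither.
- **The 0.05 is not a mistake.** This also stands. It is the correct alpha for a single comparison, and a reader who concluded that both error rates are misprinted would go too far.
- **No success rule says that one significant outcome is enough.** A reader might infer such a rule from "detecting an effect of 0.50 between groups on any of the three aspects of outcome", but the phrase can equally mean that N suffices for each outcome taken separately. The analysis section tests each outcome and reports an interval for each. If the three are separate questions, the case for familywise control is arguable. The percentages above are therefore conditional on how the results are used.
- **Multiplicity rules are often left to an analysis plan, which is not shown.** True, and the absence of such a rule is not the point made here. The article itself fixes three co-equal primary outcomes, a target worded as any of them, and an N computed at the full 0.05. A later rule could control the error, but a Bonferroni or Holm procedure would not give the planned 80% for each outcome at its first step.
- **Two models per outcome do not simply double the tests.** The article gives the unadjusted analysis some precedence by calling it the first primary analysis. The word first still leaves open whether the covariance analysis is also primary.
- **The 0.66 is not the power of the trial.** Correct. It applies to one outcome at Holm's first step. If any one of three real effects would do, power is well above it.

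**Conclusion.** The point holds in two parts of unequal weight. The Type II error is certainly misstated: it should be 0.20, and 64, 128 and 144 are unaffected. The second part is conditional. N carries no allowance for three co-equal primary outcomes, and nothing in the article limits the claim that a single significant result may support. If any one result is taken to answer Objective 1, the familywise error is 14.3% under independence and 13.6% to 8.4% over assumed correlations of 0.3 to 0.9, so it exceeds 5% throughout that range. If the three outcomes are separate questions with no overall claim, this inflation does not arise in the same way, but the protocol should then say so.

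**What to change.** 1. Change the sample-size line to power = 0.80 (Type II error = 0.20). This costs nothing.
2. Before data are seen, state one of the following:
   - a fixed testing order for the three outcomes, chosen by the investigators. The first outcome keeps power 0.80 at 0.05, and a later one can be claimed only if those before it are significant;
   - Holm across the three outcomes, with power restated as 0.66 per outcome at the first step with 64 per group (0.72 with 72), and a note that power for at least one outcome is higher;
   - that the three are separate questions, each at 0.05, and that no overall superiority claim rests on any single one.
3. State which model is confirmatory for each outcome: the unadjusted repeated-measures analysis or the covariance analysis. The other becomes supportive.

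All of this is wording and needs no extra participants. The price of Holm is a less favourable stated power; keeping 0.80 for every outcome at 0.05/3 would instead take about 192 participants. The price of a fixed order is that a non-significant early outcome blocks claims on later ones. The price of separate questions is giving up an overall claim based on one outcome.
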